## Anticipated level of statistical significance

All tests will be performed at 5%.

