| Other interventions added by the study | The intervention will not test any particular drug or medical disposal, but rather the application of the international guidelines (ESC, EUSEM, AHA) through the implementation of a protocol of care. The care bundle of early care with a checklist that includes the following checklist:   - Detection and treatment of AHF precipitating factors (infection, acute coronary syndrome or atrial fibrillation) - Treatment of congestion, including a protocol of nitrates titration, and low dose furosemide, as recommended by international guidelines - Non-invasive ventilation if indicated, as recommended by international guidelines - Preventive low molecular weight heparin, as recommended by international guidelines   During the control period, the standard of care will be treatment as usual, left at the discretion of the treating emergency physician |
| Expected benefits for the participants and for society | We anticipate a reduction in length of hospitalisation and rate of readmission. The intervention is aimed at increasing the number of days alive and at home in the first month after inclusion. This benefit for the patient should be associated with a reduction in the allocation of hospital resource. |
| Minimal risks and constraints added by the study | Minimal risk, as only recommended treatments will be administered  The intervention will not test any particular drug or medical disposal, but rather the application of the international guidelines (ESC, EUSEM, AHA) through the implementation of a protocol of care.  Validated treatment will be randomly attributed to a group of patients (List of interventions listed in the article L1122-1-2 of the French Public Health Code, and corresponding to a Minimal risks and constraints) |
| Scope of the study | Emergency care and acute heart failure |
| Number of participants included | 500patients |
| Number of sites | 15 centers in France  If one center withdraw from the trial before its start, we will invite another ED to participate (2 centers are listed as willing to participate if possible) |
| Schedule for the study | - inclusion period: 36 weeks - participation period (treatment + follow-up): 30 days - total duration: 36 weeks and 30 days |
| Number of enrolments expected per site and per month | 4 |

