## Summary of the known and foreseeable benefits and risks for the participants

Despite a small improvement in outcomes of elderly admitted for AHF within the past decades, its morbidity and mortality remains severe with a 10% rate of 30-day mortality, and 25-30% of early readmission rate.^6,7,18,29^ In the majority of cases, treatment can be initiated in the ED. However, many studies showed that a majority of these patients are still not getting recommended therapies in the ED – either for AHF *per se*, or for precipitating factors of AHF, especially acute coronary syndrome or infection.^7,16,18^

In this context, there is an urgent need of multidisciplinary management program of patients with AHF in the ED and following ED to ensure better results and adherence.^30^The great outcome improvement provided by early treatment in the ED have long been established in other settings (e.g., sepsis, myocardial infarction). Unfortunately, AHF has not been considered with this regard until recently. Some reports suggest the importance of time to introduce therapy in AHF. Data derived from ADHERE registry indicate that early treatment (<6h) in emergency departments would bear a positive impact by decreasing in-hospital mortality and morbidity rates (unadjusted OR for in-hospital mortality 0.77, adjusted OR 0.87 (95%CI [0.76 – 0.96]).^26^ Very recently, in their large prospective observational study, Matsue et al. reported a significant decreased mortality of AHF following the initiation of decongestion therapy within 1 hour in the ED (OR for in-hospital mortality of 0.39 (IC 95% [0.20-0.76]).^28^

As expressed by Januzzi and Felker in a recent editorial “***the failure of novel therapies for AHF requires us to make better use of what we already have. A systematic approach would allow an optimal management of acute HF, and in turn could finally improve outcomes.”***^31^If our hypothesis is confirmed, our trial of early intensive care bundle will be the first RCT showing a significant reduction in short term morbidity and mortality in elderly AHF, similarly to what was achieved for sepsis (with a 15% absolute reduction of in-hospital mortality).^32,33^

Lastly, it can be stressed that the observed high rate of deviation to the guidelines may be caused in part by their low level of evidence of these last one. A positive outcome of the execution of a care bundle based on these recommendations would increase physician’s adherence, and patients’ outcomes.

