## Secondary endpoints

- 30 day all-cause mortality
- 30 day cardio-vascular mortality
- Hospital readmission at 30 days
- Length of in hospital stay truncated at 30 days
- Changes of more than 2 fold in creatinine level from inclusionto day 30 or to discharge whichever comes first.

Creatinine will be measured at day 0 in the ED, and at discharge day or day30, whichever comes first.

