## Secondary evaluation criteria

In hospital mortality, all causes mortality at 30 days and cardiovascular mortality at 30 days will be compared between groups by using Pearson's chi-square test or Fisher exact test.

If possible, generalized linear regression mixed model with Poisson distribution will be performed. If the number of events is sufficient, generalized linear regression mixed model using logit link will be performed.

The length of stay in hospital in days will be compared between the two periods by using Student t-test or Wilcoxon rank-sum test as needed. If possible, a linear regression mixed model will be performed. A random effect for each cluster will be considered and considered fixed effects will be: strategy and, for the stepped wedge design, time representing each step. In case of non-normality distribution of the interest variable, a transformation could be realized.

Percentage of patients with a change of more than 2 fold in creatinine between inclusion and 30 days will be compared between groups by using Pearson's chi-square test or Fisher exact test. If possible, generalized linear regression mixed model with Poisson distribution will be performed. If the number of events is sufficient, generalized linear regression mixed model using logit link will be performed.

Second analysis will be performed on the per protocol population.

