## Calculation hypotheses for the number of subjects required and the result

From our previous cohort, the mean number of days alive and out of hospital at 30 days was 14±9. To be clinically relevant, we estimate that the new approach should increase this endpoint of 3 days at least (a relative increase of 20%). With a power of 80% and alpha=5%, we need to include 283 patients. Since this study is planned as a stepped wedge cluster and after specification of following elements: 15 clusters, ICC=0.0001, the design effect is estimated at 1.609, so we need to analyze454patients – to take into account 10% of non-evaluable patients, it is necessary to include 500 patients -around 2 per cluster for each 2 weeks period.

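### Section 13.3 makes unadjusted tests the default for the secondary endpoints of a stepped wedge trial and, with 13.5, never says which of several 5% results decides

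*Protocol*

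**What the plan says.** Section 13.2 analyses the primary endpoint, days alive and out of hospital at 30 days, by a linear mixed model with a random centre effect and fixed effects for strategy and step.

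Section 4.2 lists five secondary endpoints: all-cause death, cardiovascular death, readmission, length of stay ("Length of in hospital stay truncated at 30 days") and a more than two-fold change in creatinine.

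Section 13.3 handles them differently from the primary:

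- **Deaths.** "In hospital mortality, all causes mortality at 30 days and cardiovascular mortality at 30 days will be compared between groups" by chi-square or Fisher test. A Poisson mixed model follows if possible, and then: "If the number of events is sufficient, generalized linear regression mixed model using logit link will be performed".
- **Creatinine.** The same sequence.
- **Length of stay.** A t-test or Wilcoxon test, then a linear mixed model if possible. Only here does 13.3 spell out random centre, strategy and step.
- **Readmission.** No test is named.
- **In-hospital mortality.** Tested, although section 4.2 does not list it.
- **Per protocol.** A second analysis on that population closes the section.

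Section 13.5 consists of one sentence: "All tests will be performed at 5" per cent. No section says which of these results is decisive, and none calls the secondary results supportive or exploratory.

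**The concern.** In a stepped wedge trial the control patients come mostly from the early weeks and the intervention patients mostly from the late weeks. A comparison that ignores calendar time therefore mixes the effect of the bundle with whatever else changed over 36 weeks. Section 5.1 chose this design partly to avoid such a period effect, and section 13.2 adjusts for step accordingly. Section 13.3 does not carry that through, because the unadjusted test always runs and the adjusted model is optional.

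Two things are at stake. First, the default test can show a difference in mortality, stay or creatinine that is only a time trend, or hide a real one. Second, when the simple test and the model disagree, both have been judged at 5% and the protocol gives no rule for which to believe. In an open trial, an isolated secondary p-value below 0.05 is easily read as evidence of benefit.

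**Working it through.** **1. The primary alpha is consistent.** Section 13.4 gives "the mean number of days alive and out of hospital at 30 days was 14±9", a target difference of 3 days, and: "With a power of 80% and alpha=5%, we need to include 283 patients". The two-sided total is 4 × (1.960 + 0.842)² × 9² / 3² = 282.6, that is 283. The primary test is therefore a two-sided 5% test, and nothing below changes that.

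**2. Calendar imbalance in Figure 1.** Inputs: 15 centres, 18 fortnights, one centre switching per fortnight from weeks 5-6. Equal numbers per centre and fortnight are assumed. Centre *i* contributes *i* + 1 control fortnights and 17 − *i* intervention fortnights.

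- Control cells: Σ(*i* + 1) = 135. Intervention cells: Σ(17 − *i*) = 135.
- Sum of fortnight numbers: 815 in control cells and 1,750 in intervention cells (total 15 × 171 = 2,565).
- Mean fortnight: 815/135 = 6.04 for control and 1,750/135 = 12.96 for intervention.
- Difference 6.93 fortnights. The first and last fortnights are 17 apart, so 6.93/17 = 0.41.

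If an outcome drifts linearly by an amount D from the first to the last fortnight in all centres, the unadjusted difference in means or proportions contains 0.41 × D with no effect of the bundle. As an illustration, a drift of 1 day in length of stay would appear as 0.41 day and a drift of 2 days as 0.81 day. A linear model with a fixed effect per step removes any trend common to the centres. The size of D is unknown; the protocol gives no figure.

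**3. Two analyses of one endpoint, no trend.** With independent errors of equal variance, the correlation between the unadjusted and step-adjusted estimates is the square root of the within-step share of the variation in strategy.

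- Total variation: 270 × 0.25 = 67.5.
- Within steps: Σ *k*(15 − *k*)/15 for *k* = 1 to 15 = 560/15 = 37.33.
- Correlation: √(37.33/67.5) = 0.744. If centre is also a fixed effect, the variation left is 21.78 and the correlation is √(21.78/67.5) = 0.568.

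For two standard normal statistics with correlation 0.744, the chance that at least one exceeds 1.96 in absolute value is 8.1%. At correlation 0.568 it is 8.9%. For binary endpoints this is a large-sample approximation.

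**4. Clustering itself.** Section 13.4 assumes an ICC of 0.0001 for the primary endpoint. With 454/15 ≈ 30 patients per centre, the ordinary clustering factor is 1 + 29 × 0.0001 ≈ 1.003. On that assumption the problem is the missing step adjustment far more than the missing centre effect. No ICC is given for the secondary endpoints.

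**5. Family-wise error, for context.** Chance of at least one two-sided p < 0.05 with no true effects, one test per endpoint, equal correlation assumed:

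| Tests | Corr. 0 | 0.3 | 0.5 | 0.8 |
|---|---|---|---|---|
| 4 (listed in 4.2 with a named test) | 18.5% | 17.4% | 15.6% | 11.4% |
| 5 (all listed in 4.2) | 22.6% | 20.9% | 18.3% | 12.7% |
| 6 (plus in-hospital mortality) | 26.5% | 24.1% | 20.7% | 13.9% |

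These figures count errors in both directions. For benefit only, five independent tests give 1 − 0.975⁵ = 11.9%.

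**The case against.** **Multiplicity.** A reader might infer that the secondary endpoints run at an error rate of 18% to 21% where the protocol promises 5%. The documents do not support that. Section 13.5 sets a level per test and claims no family-wise control. Unadjusted secondary tests beside a single primary endpoint are ordinary practice, and a multiplicity rule for them is commonly left to the SAP, which is not at hand. The figure also depends on a correlation the protocol does not give. This part of the objection stands, so the lack of a hierarchy is not itself an error.

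**Confirmatory intent.** A reader might also infer that secondary claims are planned. Section 2.6 says the trial "will be the first RCT showing a significant reduction in short term morbidity and mortality in elderly AHF", but only on the condition that the hypothesis is confirmed. Morbidity and mortality together is also how the protocol describes its main objective and its composite primary endpoint. The Summary says "We anticipate a reduction in length of hospitalisation and rate of readmission", but under expected benefits, followed at once by the aim of more days alive and at home. Index stay and readmission days are components of the primary endpoint. No section rests an efficacy claim on a secondary p-value.

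**Coverage.** It would be wrong to say that every secondary endpoint is tested, since section 13.3 names no test for readmission.

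**Choice of analysis.** Section 13.3 does not permit free choice of whichever analysis is significant, and making models conditional on enough events is sensible. With 10% mortality, 454 patients give about 45 deaths, or 2.5 per fortnight, so a logit model with a term for each step may be unstable. That is a reason to name a fallback in advance. It does not justify a default that ignores time, and it hardly applies to length of stay, which every patient contributes to.

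What remains is what the text fixes: the unadjusted test comes first, the adjusted model is optional, both are judged at 5%, and neither is named as decisive.

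**Conclusion.** The point holds as a defect in how section 13.3, read with 13.5, fixes the secondary analyses. The default tests omit the step adjustment that the design needs and that section 13.2 applies to the primary endpoint. They absorb about 41% of a linear secular trend, assuming equal cell sizes and a trend common to all centres. With no trend, having two 5% results and no deciding rule lets the false-positive rate per endpoint reach about 8%, if either result may be quoted.

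The family-wise range of about 11% to 27% is context only. The primary test, its alpha and the sample size are unaffected. The mismatch between sections 4.2 and 13.3 on readmission and in-hospital mortality can be read directly from the text and needs no assumption.

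**What to change.** - **Section 13.3.** For each secondary endpoint, name one deciding analysis: the mixed model with random centre and fixed strategy and step, using one stated distribution and link, reported as an estimate with 95% CI. State these effects for the binary endpoints too. Fix in advance a simpler form of time (for example grouped steps) in case the model cannot be fitted.
- **Other analyses.** Make the unadjusted tests, the alternative models and the per-protocol repeat sensitivity analyses, with no separate claim at 5%.
- **Section 13.5.** Limit the confirmatory two-sided 5% test to the strategy effect on the primary endpoint in the ITT population, and call the secondary results supportive.
- **Sections 4.2 and 13.3.** Name an analysis for readmission, and either list in-hospital mortality as a secondary endpoint or drop its test.

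A fixed order or a Holm procedure after a significant primary result is optional, and is needed only if the sponsor wants a confirmatory claim on a secondary endpoint.

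The cost is a few sentences, with no extra patients, data or procedures and no change to the primary analysis. The downside is that an isolated secondary p < 0.05 could no longer be presented as a confirmed effect.

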## Statistical criteria for termination of the study

Not applicable.

## Method for taking into account missing, unused or invalid data

Missing value for the principal criteria will be considered as failure (0 days alive and out of the hospital), whatever the period considered.

Sensitivity analyses will be performed to check the impact of replacement methods of missing values with missing data considered: 1) success (maximum days alive and out of the hospital observed in the total population of the study) in the experimental group and as failure (0 days alive and out of the hospital) in the control group; 2) failure in the experimental group and as success in the control group.

Others missing data will not be replaced.

- 1. Management of modifications made to the analysis plan for the initial strategy

Modification made in analysis will be documented in the final report.

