# SCIENTIFIC JUSTIFICATION FOR THE RESEARCH

## CURRENT KNOWLEDGE

Acute heart failure (AHF) is a syndrome defined as new-onset or worsening of symptoms and signs of HF,often requiring rapid escalation of therapy and hospital admission. The clinical presentation of AHF typically includes symptoms or signs related to congestion and volume overload rather than to hypoperfusion.^1^ Acute heart failure represents 5% of all emergency hospitalizations, and is the most common primary diagnosis in patients ≥75 years visiting the ED.^2,3^ The ED are the main entry to the hospital for AHF, with 64% of these admissions being subsequent to an ED visit.^4^ This syndrome is reportedly associated with poor outcomes, with a 80% rate of hospital admission, a median length of hospital stay of 10 days and a mortality around 10% at 30 days, and a readmission rate of 25-30% at 30 days.^5–7^

Despite a high rate of morbidity and mortality, the management of AHF has not changed for several decades and most clinical studies failed to demonstrate a positive impact of new drugs on patients’ prognosis.^8,9^European guidelines include the use of diuretics, nitrates, oxygen and non-invasive ventilation (NIV) when indicated along with the treatment of any potential AHF triggers (precipitating factors).However, these guidelines are based on moderate levels of evidence (IB and IIaB), and high-quality randomized controlled trials data (RCT) are lacking.^10–12^

In 1998 and 2000, the two cornerstones trials of Cotter et al. provided evidences of benefits associated with early vasodilatator therapy with nitrates, although on a very small sample of patients (less than 200 in total).^13,14^ Since then, every prospective trial on AHF management failed to report a clinical significant improvement of outcomes. Equipoise remains on many questions regarding the recommended therapeutics: the optimum dose and route of administration of diuretics are not clear, the use of nitrates is also debated, and the benefit of non-invasive ventilation (NIV) is unclear.^15–17^

Despite these controversies, recommendations and guidelines are published by international society (ESC, AHA, …) and constitute the basis of our understanding and standard of care.^10,11^ However, a large proportion of elderly patients in AHF do not receive adequate care, including low rate (30-50%) of nitrates therapy.^7,18,19^

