# EFFICACY ASSESSMENt

## Description of parameters for assessing efficacy endpoints

The primary endpoint (days alive and out of hospital at day 30) will be measured at the end of the 30 days follow up period, either by hospital visit, phone interview, and medical chart review. Vital status, date of death and date of discharge will be collected.

A death during the follow up period will correspond to 0. An ED visit will correspond to “one day” at the hospital.

For example, a patient not admitted (at day 0), with no return visit to the hospital, and alive at day 30 will have 30 days alive and out of hospital.

A patient who is admitted (at day 0) and stays 8 days in the hospital before being discharged and have no readmission and no return visit to the ED would have a “22 days alive and out of hospital at 30 days”.

A patient that is admitted and die at 13 days, either at home or in hospital will have 0.

A patient that is admitted for 10 days, discharged home for 5 days then admitted at day 16 for 15 days will have 5 days alive and out of hospital (namely day 11, 12, 13, 14 and 15).

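### Section 13.7 checks a missing primary endpoint only at two opposite extremes; above about 3% missing the pair says little about plausible departures from the missing = 0 rule

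*Protocol*

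**What the plan says.** Protocol 13.7 sets a missing primary endpoint to 0 days in either period, then names two sensitivity analyses:

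- Analysis 1 treats missing values as "success (maximum days alive and out of the hospital observed in the total population of the study) in the experimental group and as failure" in the control group.
- Analysis 2 treats them as "failure in the experimental group and as success in the control group".

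Other parts of the protocol bear on this:

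- 13.4 takes a control value in which "the mean number of days alive and out of hospital at 30 days was 14±9", a target gain of 3 days, and a margin: "to take into account 10% of non-evaluable patients, it is necessary to include 500 patients".
- 9.1 scores a patient who is not admitted, does not return and is alive at day 30 as 30 days. A patient who "stays 8 days in the hospital before being discharged and have no readmission and no return visit to the ED would have a" score of 22.
- 2.1 describes "a 80% rate of hospital admission, a median length of hospital stay of 10 days".
- 13.9 keeps every included patient in the ITT set. It removes patients with a missing primary endpoint from the per-protocol set, together with other major deviations. 13.3 announces a second analysis on that set.

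**The concern.** The primary rule gives a patient with unknown outcome the same score as a patient who died. That is a strong assumption, and the sensitivity analyses should show whether a reasonable departure from it would change the conclusion.

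The two named scenarios instead assume that missing patients did as well as possible in one period and as badly as possible in the other. How far each result moves depends only on the fraction missing, not on anything observed. If that movement is as large as the effect the trial is built to detect, the two results will tend to disagree whatever the truth is. A reader then learns nothing about the plausible cases in between, and a genuine benefit could be reported as not robust.

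The success value makes the bounds wider than they need to be. Most patients are expected to be admitted, and an admitted patient cannot reach 30 days.

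**Working it through.** **1. The plan's own sample size.** With a difference of 3, SD 9, two-sided 5% (two-sided is assumed; the protocol does not say) and 80% power, the total is 4 × [9 × (1.96 + 0.84)/3]² ≈ 282.6. This agrees with "With a power of 80% and alpha=5%, we need to include 283 patients". Then 282.6 × 1.609 ≈ 454.6 (stated: 454) and 454 × 1.1 = 499.4, so 500. The inputs are therefore read correctly. The inflation implies 46/500 = 9.2% non-evaluable, close to the stated 10%.

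**2. Shift from the primary handling.** Let m be the fraction missing, equal in both periods, and let the observed maximum be 30 (the score in the 9.1 example).

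- Analysis 1 minus primary = m × (30 − 0) = +30m
- Analysis 2 minus primary = −30m

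At m = 0.10 this is ±3.0 days; at 9.2% it is ±2.76. With a maximum of 29, the shift at 10% is 2.9. If the missing rates differ, each analysis shifts by 30 times the rate in the group set to the maximum.

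**3. Expected results under a true effect of 3 days**, missing at random:

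- Primary: 3(1 − m)
- Analysis 2: 3(1 − m) − 30m = 3 − 33m

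At m = 0.10 the primary expects +2.7 days and analysis 2 expects −0.3 days.

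**4. Standard error.** In a group with observed mean μ and imputed value v, the mean is M = (1 − m)μ + mv and the variance is (1 − m)(9² + μ²) + mv² − M². SE = √[(V₁ + V₂)/250 × 1.609], with 250 patients per period. The even split follows from Figure 1: reading its pattern across the omitted columns, 135 of 270 centre-fortnights are intervention.

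Example, analysis 1, no effect, m = 0.10:

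- Intervention: M = 0.9 × 14 + 0.1 × 30 = 15.6; V = 0.9 × 277 + 90 − 15.6² = 95.9
- Control: M = 12.6; V = 249.3 − 12.6² = 90.5
- SE = √(186.5/250 × 1.609) = 1.10; z = 3.0/1.10 ≈ 2.7; chance of a significant result about 78%

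**5. By missing rate**

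| Missing | Shift (days) | No effect: chance analysis 1 is significant for benefit (same for harm in analysis 2) | True +3: primary expects | True +3: analysis 2 expects (SE) | True +3: chance analysis 2 is significant for benefit |
|---|---|---|---|---|---|
| 2% | 0.6 | 8% | 2.94 | 2.34 (1.04) | 61% |
| 3% | 0.9 | 14% | 2.91 | 2.01 (1.06) | 48% |
| 5% | 1.5 | 29% | 2.85 | 1.35 (1.08) | 24% |
| 7% | 2.1 | 50% | 2.79 | 0.69 (1.09) | 9% |
| 10% | 3.0 | 78% | 2.70 | −0.30 (1.12) | 1% |

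The expected analysis 2 estimate falls below 1.96 SE at about 3% missing. At 10% missing, a true effect of about 5.9 days is needed before analysis 2 is expected to show significant benefit.

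**6. Check by simulation.** On the 15-centre, 18-fortnight layout with N = 500, period effects and negligible clustering, analyses 1 and 2 were falsely significant in 71% and 74% of trials at 10% missing, 25–26% at 5% and 7–8% at 2%. With fixed centre effects and an SD of about 8.5, the 10% figures were 51–52%. Neither model is exactly the random-centre model of 13.2. The shift itself does not depend on the model.

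**7. The success value.** By 9.1, 8 hospital days cap the score at 30 − 8 = 22, and a 10-day stay caps it at 20. As an illustration, suppose missing patients follow 2.1, with 80% admitted, 10 days taken as the typical stay, and that stay fully documented. The average attainable maximum is then 0.8 × 20 + 0.2 × 30 = 22, and the shift at 10% missing is 2.2 days, not 3.0. Capping tightens the bounds but does not fill the gap between them.

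**The case against.** A best-case/worst-case pair is a recognised device that is meant to be extreme. Section 13.7 attaches no rule by which either result confirms or overturns the primary conclusion. If both bounds agree with the primary result, that is strong evidence of robustness. This stands, so the percentages in the table describe how the bounds behave. They are not error rates of the trial.

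The 10% in 13.4 is a planning margin for non-evaluable patients, not a forecast of missing endpoints. Sections 6.1 and 9.2 plan chart review, calls to patients and relatives, the family practitioner, hospital databases and, as a last resort, the city hall. The city hall would reveal a death, which settles the score at 0, but not days in hospital. This also stands: at about 2% missing the bounds move by only 0.6 days and are usable.

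The per-protocol analysis uses no imputed primary endpoint. It is a partial check, because it also removes selection failures, crossovers and other major deviations.

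Index-stay dates may not always be usable. Under 8.1, only data collected before a patient's exit can be used, so the cap can apply only to days already documented.

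Imputation models are commonly left to a statistical analysis plan, and one may exist. Their absence here is not the point. The point is that 13.7 fixes two particular scenarios and a particular success value.

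A reader might go further and infer that the two analyses cannot check the primary result at all, or that a true benefit would always look non-robust. The documents do not support either. Both depend on the missing rate, which the protocol does not predict, and significance in the wrong direction is frequent at 10% missing but not certain.

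**Conclusion.** The point holds in a limited form. Section 13.7's two missing-data analyses are valid outer bounds with no plausible scenario between them. They differ from the primary handling by 30 days times the missing rate, which equals the 3-day target only if missingness reaches about 10%. Above roughly 3% missing, a true 3-day effect would not be expected to stay significant in analysis 2. From there on the pair says little about reasonable departures from scoring missing as 0.

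Separately, and at any missing rate, the success value contradicts the scoring in 9.1 for patients with documented hospital days.

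The figures assume equal missing rates in the two periods, data missing at random, an observed maximum of 30, the 14 ± 9 of 13.4 and the stated design effect. The primary analysis is not affected. This is a cheap improvement, not an error that invalidates the plan.

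**What to change.** Revise 13.7 as follows, leaving the primary rule as it is.

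1. Keep the best-case/worst-case pair, but label it as descriptive bounds and make no significance claim from it.
2. Cap each patient's success value at 30 minus the hospital days already documented and usable for that patient.
3. Add one intermediate check: multiple imputation of the primary endpoint from period, step, centre, baseline data and available stay dates.
4. Build a delta-adjusted (tipping-point) analysis on that imputation. Lower the imputed values in the intervention period, and separately in the control period, in fixed steps such as 1 day. Report the shift at which the conclusion changes.

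The cost is revised wording in 13.7 (or in the statistical analysis plan, with a reference from 13.7) and a little more programming. No extra data or patients are needed. The downside is a range to interpret in place of two p-values.
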